**Primary analysis:**

- Very preterm with cognitive deficits Vs. Very preterm without cognitive deficits
- Moderately preterm with cognitive deficits Vs. Moderately preterm without cognitive deficits

**Secondary analysis:**

- Very preterm with cognitive deficits Vs. full-term without cognitive deficits
- Moderately preterm with cognitive deficits Vs. full-term without cognitive deficits

All models will be adjusted for above-mentioned confounders/covariates.

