**Study Information**

**Overall research question**

Why are children born preterm, particularly those born before 34 weeks, at a higher risk for cognitive deficits during mid-childhood?

This research question is based on our previous findings, where we observed that children born before 34 weeks had lower composite cognitive scores compared to their full-term peers at 9-10 years of age. This association was independent of genetic, maternal, neonatal, and child factors.

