**Hypotheses**

Children born before 34 weeks with cognitive deficits will show mixed patterns of cortical thickness (i.e., thinner in primary sensory hubs and thicker in higher-order cognitive hubs) and smaller subcortical volumes at 10 years of age compared to both children born before 34 weeks without cognitive deficits and those born at term without cognitive deficits.

We expect higher structural covariance (stronger connection/coordination) in primary sensory networks and lower structural covariance (weaker connection/coordination) in higher-order networks in children born before 34 weeks with cognitive deficits.

We will extract individual structural covariance values only for the networks that show significant differences in the primary analysis and explore their relationship with behavioral outcomes, such as ASD and ADHD symptoms at 12 years of age.

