**Cognitive outcomes**

The neurocognitive battery, designed for completion in 70 minutes, began with Snellen vision chart to assess visual acuity, excluding children with legal blindness. The battery includes ten measures, seven from NIH Toolbox: Picture Vocabulary, Oral Reading Recognition, Pattern Comparison, Processing Speed, List-Sorting Working Memory, Picture Sequence Memory, Flanker, and Dimensional Change Card Sort. The ABCD study team also assessed Little Man Task (LMT) and Rey Auditory Verbal Learning Test (RAVLT). All tests were administered on an iPad with one-on-one monitoring by a research-assistant.

Cognitive deficit will be defined as a score between 1-2 standard deviation below the control group mean, based on the fully age-corrected composite score from the NIH Toolbox.

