**Constructing of Structural Covariance Networks (SCN):**

To investigate SCN, Pearson partial correlation analysis will be conducted on the brain hubs. This analysis will be performed separately for groups: children born preterm with cognitive deficits, children born preterm without cognitive deficits, and children born at-term with normal cognitive function.

In the first step, we will calculate correlation coefficients between each pair of regions within the specified volumes for each group. These correlations will be adjusted for potential confounding variables, including age, sex, socioeconomic status (SES). To control for multiple comparisons, FDR correction will be applied when assessing significant structural covariance between each pair of cortical regions.

In the second step, Fisher’s r-to-z transformation will be applied to the significant structural covariance connections to standardize the correlation coefficients.

Finally, we will assess between-group differences in cognitive structural covariance networks using a z-test. Specifically, we will compare the networks of preterm children with cognitive deficits against those of preterm children without cognitive deficits, and against those of term-born children with normal cognitive function.

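### No planned analysis includes full-term children with cognitive deficits, so the plan cannot show whether a brain pattern is specific to preterm deficits or common to low cognition at any gestational age

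*SAP*

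**What the plan says.** The overall research question is "Why are children born preterm, particularly those born before 34 weeks, at a higher risk for cognitive deficits during mid-childhood". The Hypotheses section is narrower. It concerns children born before 34 weeks with deficits "compared to both children born before 34 weeks without cognitive deficits and those born at term without cognitive deficits".

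The Analysis section sets a general aim of comparing brain structure in children with and without deficits. The contrasts then listed are:

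- Primary: "Very preterm with cognitive deficits Vs. Very preterm without cognitive deficits" and "Moderately preterm with cognitive deficits Vs. Moderately preterm without cognitive deficits".
- Secondary: "Very preterm with cognitive deficits Vs. full-term without cognitive deficits" and "Moderately preterm with cognitive deficits Vs. full-term without cognitive deficits".

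The SCN section forms three groups: "children born preterm with cognitive deficits, children born preterm without cognitive deficits, and children born at-term with normal cognitive function". The Sensitivity analysis section lists one interaction, between group and socio-economic status. Under Cognitive outcomes, "Cognitive deficit will be defined as a score between 1-2 standard deviation below the control group mean", using the age-corrected NIH Toolbox composite.

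**The concern.** Gestational group and deficit status define a two-way layout, and one cell, full-term with deficit, is never used. This has two consequences.

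- The secondary contrasts change both factors at once. A difference could reflect prematurity, low cognition or both.
- The primary contrasts hold gestational stratum fixed, but they would also be non-zero if the measure were related to cognition in the same way in all children. Nothing in the plan shows what happens at term.

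The point at stake is interpretation. All four contrasts could be significant although the deficit pattern is the same in full-term children. The SCN comparisons have the same gap, and the networks they select go on to the behavioural analysis.

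**Working it through.** The SAP gives no power, sample-size or cell-size figure for these contrasts, so there is no stated figure to reproduce. The check asks which quantities the contrasts identify, and then what the missing cell would contribute.

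**1. Identifiability.** Write PD and PN for preterm with and without deficit, and TD and TN for full-term with and without deficit. The argument applies to each preterm stratum. The plan estimates PD − PN (primary) and PD − TN (secondary).

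| Quantity | Available from the plan? |
|---|---|
| Deficit association within preterm, PD − PN | Yes, directly |
| Prematurity association without deficit, PN − TN | Only by subtraction: (PD − TN) − (PD − PN); not listed |
| Deficit association at term, TD − TN | No |
| Prematurity association with deficit, PD − TD | No |
| Interaction, (PD − PN) − (TD − TN) | No |

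The last three involve TD, which no planned contrast contains. The subtraction is exact for cell means; it is only approximate if the contrasts come from separately adjusted models.

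**2. Illustration (assumed means, SD units).** Take PD = −0.5, PN = −0.2, TN = 0.

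- Same deficit pattern at term, TD = −0.3: PD − PN = −0.3; PD − TN = −0.5; interaction = −0.3 − (−0.3) = 0.
- Pattern confined to preterm children, TD = 0: PD − PN = −0.3; PD − TN = −0.5; interaction = −0.3 − 0 = −0.3.

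The planned results are identical in the two cases.

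**3. Size of the unused cell.** Assume normal scores and that the control group in the deficit definition is the full-term group. The share 1 to 2 SD below the mean is Φ(−1) − Φ(−2) = 0.1587 − 0.0228 = 0.1359. The SAP gives a cohort of 11,875 but no full-term count. Assumed counts of 2,000, 4,000 and 6,000 give about 272, 544 and 815 full-term children with deficits.

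**4. Precision of the interaction.** Assume cells of 60 with and 240 without deficit (preterm, strata pooled), 400 with and 2,500 without (full-term), unit residual SD and no covariate adjustment.

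- Within-preterm contrast: variance 1/60 + 1/240 = 0.0208; SE = 0.144.
- Interaction: variance 0.0208 + 1/400 + 1/2,500 = 0.0237; SE = 0.154.
- SE ratio: 0.154/0.144 = 1.07.
- Detectable at 80% power, two-sided 5%: (1.96 + 0.84) × 0.154 = 0.43 SD.
- Power for an interaction of 0.2 SD: 0.2/0.154 = 1.30; Φ(1.30 − 1.96) ≈ 25%.

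The full-term cells add little variance. The limit is the size of the preterm cells, so each stratum analysed separately would be less precise.

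**The case against.** The strongest defence is that the plan tests what it hypothesises. The Hypotheses section names two comparators, preterm without deficits and term without deficits, and the regression and SCN analyses use both. It states no hypothesis that the pattern is specific to preterm children. This stands.

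A reader might go further and infer that none of the contrasts separates prematurity from low cognition. The document does not support that. The primary contrasts compare children within one gestational stratum, and the prematurity difference among children without deficits follows by subtraction. Only the secondary contrasts mix the two factors.

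A reader might also infer that the missing cell alone prevents an answer to the research question, or that only a significant interaction could provide one. That does not follow either. Prematurity could shift a brain measure that relates to cognition equally in all children; this would help to explain the excess risk with zero interaction. Nor would the extra cell by itself make the design explanatory, since MRI and cognition are both measured at 9–10 years.

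Finally, a 7% larger SE says nothing about power. With about 25% power for 0.2 SD on the assumed cells, making the interaction a condition for any claim would be a poor rule. This also stands.

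None of this supplies the missing comparison. A shared pathway also implies that the deficit association is present at term, and the plan has no estimate of it.

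**Conclusion.** The point holds in a limited form. The secondary contrasts mix prematurity with deficit status, and no planned regression or SCN comparison can distinguish a brain pattern specific to preterm deficits from one common to low cognition at any gestational age. This limits how far the results can answer the research question. It does not invalidate the primary contrasts or the two comparisons named in the hypothesis.

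The identifiability result needs no assumed figures; it follows from the listed contrasts and groups. The −0.3 and −0.5 SD illustration, the count of roughly 270 to 815 children and the interaction SE of about 0.15 SD rest on the assumptions shown, because the SAP gives no cell sizes. It is a low-cost improvement that changes what the study may conclude.

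**What to change.** - Fit one regression per brain measure with gestational group (very preterm, moderately preterm, full-term) × deficit status and the stated covariates, including full-term children with deficits.
- Keep the four listed contrasts in their present primary and secondary roles.
- Add full-term with v without deficits, preterm v full-term without deficits, and the gestation × deficit interaction, reported as an estimate with 95% CI.
- Add full-term children with deficits as a fourth SCN group.
- State that preterm specificity will not be claimed from the four listed contrasts alone, and that a non-significant interaction will not be read as evidence that brain structure does not explain the preterm risk.

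The cost is SAP wording, some further analysis and a few more tests in the multiplicity family. Under the SAP's own deficit definition these children should already be in the cohort. The interaction will be imprecise, more so within each preterm stratum, so its interval should carry the interpretation. The SAP places registration before analysis, so a change made now is prespecified. If the group is not added, the SAP should say that the results describe differences between the named groups and do not show preterm specificity.

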**Sensitivity analysis:**

No neonatal complications (yes/no)

Poor intrauterine growth (birthweight-z score as proxy, < 1SD)

Environmental interaction (groups x SES)

**Constructing of Structural Covariance Networks (SCN):**

To investigate SCN, Pearson partial correlation analysis will be conducted on the brain hubs. This analysis will be performed separately for groups: children born preterm with cognitive deficits, children born preterm without cognitive deficits, and children born at-term with normal cognitive function.

In the first step, we will calculate correlation coefficients between each pair of regions within the specified volumes for each group. These correlations will be adjusted for potential confounding variables, including age, sex, socioeconomic status (SES). To control for multiple comparisons, FDR correction will be applied when assessing significant structural covariance between each pair of cortical regions.

In the second step, Fisher’s r-to-z transformation will be applied to the significant structural covariance connections to standardize the correlation coefficients.

Finally, we will assess between-group differences in cognitive structural covariance networks using a z-test. Specifically, we will compare the networks of preterm children with cognitive deficits against those of preterm children without cognitive deficits, and against those of term-born children with normal cognitive function.

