**Sample size**

This longitudinal cohort consists of 11,875 children, enrolled at baseline (9-10 years) and followed up annually at 21 research sites across the United States. Children were excluded if they were born extremely preterm (< 28 weeks), had a birth weight below 1200g, were not proficient in English, had neurological problems, a history of seizures, or a contraindication for undergoing brain magnetic resonance imaging (MRI) scans.

Since ABCD cohort includes twins and siblings, we will randomly select one child per family to eliminate this source of bias.

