**Exposure**

Moderately preterm (32 - 34 weeks)

Very preterm (< 32 weeks)

Full-term (39 – 40 weeks)

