**Covariates**

Age at time of MR scan, Sex, Socio-economic status (maternal education, household income, and neighbor area index), and scanner sites. These variables were selected as they known to be associated with cognitive outcomes or brain development.

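### The covariance networks pool very and moderately preterm children whom the regressions keep apart, and neither analysis adjusts for gestational age in weeks

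*SAP*

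**What the plan says.** - **Exposure** defines two preterm categories, "Very preterm (< 32 weeks" and "Moderately preterm (32 - 34 weeks", plus a full-term group. **Sample size** excludes children "born extremely preterm (< 28 weeks", so the preterm range starts at 28 weeks.
- **Primary analysis** contrasts deficit with no deficit inside each category, for example "Very preterm with cognitive deficits Vs. Very preterm without cognitive deficits". The two categories are never mixed.
- **Covariates** lists "Age at time of MR scan, Sex, Socio-economic status (maternal education, household income, and neighbor area index), and scanner sites". **Secondary analysis** extends this list to every regression: "All models will be adjusted for above-mentioned confounders/covariates".
- **Constructing of Structural Covariance Networks (SCN)** drops the split. Its preterm groups are "children born preterm with cognitive deficits, children born preterm without cognitive deficits". On adjustment it says "These correlations will be adjusted for potential confounding variables, including age, sex, socioeconomic status (SES".
- **Sensitivity analysis** covers neonatal complications, growth by birthweight z-score, and interaction with socio-economic status. Growth for gestation is not degree of prematurity, so none of these adjusts for gestational age.

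**The concern.** Gestational age is fixed before either the scan or the cognitive test and may influence both. For a deficit versus no-deficit contrast among preterm children it is therefore a candidate confounder, not a step on the path between the two. If children with deficits were born earlier on average, part of a brain difference could reflect how preterm they were rather than what accompanies the deficit.

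The regressions limit this by splitting at 32 weeks. The network analysis removes that protection without giving a reason. There the mechanism is different. Correlations are computed within each group, so a gap in mean gestational age does not enter them. What enters is the spread of gestational age inside each group. If two regions both vary with gestational age, it adds variance that they share and raises their correlation. When the two groups have different spreads, the rise differs between them.

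The consequence could carry forward, because individual covariance values are taken only from networks that show group differences and are then related to behaviour at 12 years.

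**Working it through.** The SAP gives no sample size for these contrasts, no effect size and no gestational-age distribution by deficit status, so there is no planned figure to reproduce. The omission itself is settled by reading the sections set out above. The size can only be illustrated.

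**Inputs from the SAP.** Gestation from 28 weeks; strata 28 to 31 and 32 to 34 completed weeks; deficit starting 1 SD below the control mean.

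**Assumed inputs.**
- Shares at weeks 28 to 34 of 5, 6, 9, 12, 17, 21 and 30%.
- Cognition = −b × (39.5 − weeks) + N(0,1).
- Each brain measure = −a × (39.5 − weeks) + N(0,1), independent of cognition given weeks.
- a = b = 0.05, 0.10 or 0.15 SD per week.
- Deficit = cognition below −1, with no lower limit.
- Correlation between two regions, given gestational age, of 0.30.

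**Formulas.**
- Spurious mean difference in a stratum = a × gap, where gap is the difference in mean weeks between the no-deficit and deficit groups.
- Correlation in a group whose gestational age has variance v: r = (0.30 + a²v) / (1 + a²v). Fisher z = atanh(r).

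**Results.**

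| Slope | Very preterm: gap, spurious difference | Moderately preterm: gap, spurious difference | Pooled v: deficit, no deficit | Pooled r: deficit, no deficit | Fisher-z difference |
|---|---|---|---|---|---|
| 0.05 | 0.098 wk, 0.005 SD | 0.056 wk, 0.003 SD | 3.45, 3.11 | 0.306, 0.305 | 0.0007 |
| 0.10 | 0.187 wk, 0.019 SD | 0.107 wk, 0.011 SD | 3.54, 2.89 | 0.324, 0.320 | 0.005 |
| 0.15 | 0.280 wk, 0.042 SD | 0.156 wk, 0.023 SD | 3.54, 2.54 | 0.352, 0.338 | 0.016 |

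Bottom row in full:
- Very preterm: 0.15 × 0.280 = 0.042. Moderately preterm: 0.15 × 0.156 = 0.023.
- Networks: a² = 0.0225. Deficit group: 0.0225 × 3.535 = 0.0795, r = 0.3795/1.0795 = 0.3516, z = 0.367. No-deficit group: 0.0225 × 2.540 = 0.0572, r = 0.3572/1.0572 = 0.338, z = 0.352. The difference is about 0.016.

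**Changing the assumptions, at slope 0.15.**
- Equal shares at every week: very preterm 0.15 × 0.306 = 0.046 SD; moderately preterm 0.15 × 0.159 = 0.024 SD; Fisher-z difference 0.002.
- The SAP's 1 to 2 SD band, with children below 2 SD in neither group: 0.15 × 0.190 = 0.029 SD, 0.15 × 0.123 = 0.018 SD, and 0.012 in Fisher z.
- Moderately preterm taken as 32 to 33 weeks, as the research question's limit of under 34 weeks would imply: 0.15 × 0.059 = 0.009 SD.
- Cognition slope of zero: every gap and difference is zero.
- The network sign is not fixed. With equal shares, the 1 to 2 SD band and mean cognition of −0.2 SD at 34 weeks, v is 3.75 with deficit and 3.85 without, and the Fisher-z difference is −0.0015.

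**Against sampling error.** For assumed groups of 50 and 150, the standard error of a Fisher-z difference is √(1/47 + 1/147) = 0.168, ignoring the few degrees of freedom used by covariates. The largest network effect is 0.016/0.168, about a tenth of one standard error.

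**The case against.** The strongest reply is that the SAP already handles prematurity where it compares means. Strata two to four weeks wide leave little gestational-age difference to confound anything, and a linear term inside them is a refinement. This stands for the regressions and is why the stratum figures are small. It does not explain why the networks abandon the same split.

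A second reply is that the network adjustment list is introduced as non-exhaustive, so gestational age is not formally ruled out. That is true, but a pre-registered plan should not leave an obvious candidate confounder to later choice.

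A third is that the research question reports lower cognition under 34 weeks than at full term and gives no gradient within preterm children. That also stands: the imbalance is an expectation, not a documented fact.

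Three stronger readings are tempting, and the SAP supports none of them:
- A reader might infer that the network step largely compares earlier-born with later-born children. It compares within-group correlations, which a shift in mean gestational age leaves unchanged.
- A reader might infer a bias of up to 0.11 SD from the pooled groups (gap 0.740 weeks × 0.15 = 0.111). That is a difference in pooled means, which the SAP never tests. The same assumptions put 54% of preterm children in the deficit group, which nothing in the SAP supports.
- A reader might infer that the bias favours the hypotheses. These predict mixed directions: thinner sensory and thicker higher-order cortex, and higher sensory and lower higher-order covariance. A single downward slope cannot produce that pattern.

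**Conclusion.** The inconsistency is real. The primary regressions separate the two preterm categories, the networks merge them, and gestational age in weeks is named as a covariate in neither. The likely consequence is small: at most about 0.045 SD in the very preterm stratum (0.042 to 0.046 across the assumed distributions), about 0.023 SD in the moderately preterm stratum, and about 0.016 in Fisher z. These sizes rest on an assumed cognition gradient within the preterm range, linear effects of gestational age and a base correlation of 0.30. If covariance itself changed with gestational age, the network effect could be larger and a linear term would not fully remove it; the SAP gives no information on that. Minor priority, worth doing because it is nearly free and makes the within-preterm contrast easier to interpret.

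**What to change.** - Add gestational age in completed weeks to the models under Primary analysis and to the partial correlations for the two preterm groups in the SCN section. Under the linear model above this reduces the spurious differences to zero by construction.
- Leave it out of the contrasts with full-term children under Secondary analysis, where it defines the groups. For the network comparison with term-born children, state whether the same adjusted preterm network is used. Partialling within a group does not remove the preterm versus term contrast.
- Report the distribution of gestational age for each deficit and no-deficit group.
- Give networks separately for very and moderately preterm children as a sensitivity analysis where numbers allow. This addresses covariance that changes with gestational age.
- Reconcile the under-34-weeks population in the research question and hypotheses with the 32 to 34 week category under Exposure.

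The cost is a change of wording, since gestational age already defines the exposure groups. The analysis loses one degree of freedom per model, and the stratum-specific networks will be imprecise and should be labelled as such.

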**Outcomes**

Primary outcomes: Primary networks (sensory, visual, and limbic)

Secondary outcomes: Higher-order networks (salience network, dorsal attention network, default mode network, fronto-parietal network)

Brain hubs corresponding to the mentioned networks will be studied

Cortical thickness from DK atlas and subcortical volumes will be used.

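### The structural covariance comparison has no term for overall cortical thickness and no contrast between networks, so a higher or a lower result in one set of networks cannot by itself be read as network-specific

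*SAP*

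**What the plan says.** The Hypotheses section makes a prediction with two halves of opposite sign for preterm children with deficits: "We expect higher structural covariance (stronger connection/coordination) in primary sensory networks and lower structural covariance (weaker connection/coordination) in higher-order networks".

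The Outcomes section makes both sets of networks outcomes: "Primary outcomes: Primary networks (sensory, visual, and limbic") and "Secondary outcomes: Higher-order networks (salience network, dorsal attention network, default mode network, fronto-parietal network"). On the measures it says "Cortical thickness from DK atlas and subcortical volumes will be used". No normalisation for overall thickness or brain size is mentioned.

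Under Constructing of Structural Covariance Networks, "we will calculate correlation coefficients between each pair of regions within the specified volumes for each group". On adjustment: "These correlations will be adjusted for potential confounding variables, including age, sex, socioeconomic status (SES"). The last step is "Finally, we will assess between-group differences in cognitive structural covariance networks using a z-test".

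The general list under Covariates is "Age at time of MR scan, Sex, Socio-economic status (maternal education, household income, and neighbor area index), and scanner sites". Site is on that list but is not named for the network correlations. Mean thickness, total brain size and intracranial volume appear on neither list, nor under Sensitivity analysis.

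**The concern.** A correlation between two regional thickness values across children contains a part shared by the whole cortex. The size of that part depends on how much overall thickness varies within the group. Because correlations are computed separately in each group, a difference between groups in that spread alters all of them, even if every network is organised identically.

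The z-test compares each network's correlations between groups. Nothing in the plan compares the group difference in one set of networks with that in the other, so no planned test separates a whole-cortex change from a network change.

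The primary networks carry the primary outcome. A rise there could be reported as stronger coordination when only the overall spread differs. The Hypotheses section also carries only networks with significant differences into the exploratory 12-year behavioural analysis, so a misread difference would help to choose those networks.

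**Working it through.** The SAP gives no group size, variance, power or expected correlation for this analysis, so there is no figure of its own to reproduce. The check is on the mechanism. **All variances, SD ratios and group sizes below are assumptions.**

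**Model.** Regional thickness = global part (variance G) + network part (W) + residual (e), with G + W + e = 1 in the comparison group. Let k be the ratio of the global SD in the deficit group to that in the comparison group. Within a network,

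r = (G·k² + W) / (G·k² + W + e), and the shift is atanh(r at k) − atanh(r at 1).

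**Worked case, G = 0.30, W = 0.15, e = 0.55.** At k = 1, r = 0.45.
- k = 1.2: (0.432 + 0.15)/(0.432 + 0.70) = 0.514; shift +0.084.
- k = 1.3: (0.507 + 0.15)/(0.507 + 0.70) = 0.544; shift +0.126.
- k = 1.5: (0.675 + 0.15)/(0.675 + 0.70) = 0.600; shift +0.208.
- k = 0.8: (0.192 + 0.15)/(0.192 + 0.70) = 0.383; shift −0.081.

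At k = 1.3 the shift runs from 0.093 (G = 0.20) to 0.152 (G = 0.40). With G = 0.40, W = 0.10, e = 0.50, it is atanh(0.776/1.276) − atanh(0.50) = 0.157.

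**Chance of a false edge.** The standard error is √(1/(n₁−3−q) + 1/(n₂−3−q)), with q = 5 covariate degrees of freedom. For 100 versus 300 children: √(1/92 + 1/292) = 0.120. A shift of 0.126 is then about 1.05 standard errors, and a two-sided 5% test rejects 18% of the time. With 30 versus 100 it rejects 8%; with 100 versus 3,000, 22%.

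**Simulation 1.** 7 networks of 8 regions (3 treated as sensory, 4 as higher-order), G = 0.30, W = 0.15, 100 versus 300 children, 400 runs, each pair tested at two-sided 5% before any FDR step. The true effect is network SDs of 1.4 times (sensory) and 0.6 times (higher-order) the comparison group's.

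| Scenario | Sensory z difference, unadjusted | Higher-order, unadjusted | Sensory, mean thickness removed | Higher-order, mean thickness removed |
|---|---|---|---|---|
| No true difference, k = 1.3 | +0.128 | +0.126 | 0.00 | 0.00 |
| No true difference, k = 1.5 | +0.204 | +0.205 | 0.00 | 0.00 |
| True sensory rise and higher-order fall, k = 1 | +0.093 | −0.071 | +0.118 | −0.094 |
| Same true effect, k = 1.3 | +0.198 | **+0.072** | +0.117 | −0.094 |

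With no true difference and k = 1.3, about 19% of pairs are significantly higher in both sets of networks (nominal 2.5%), and about 0.1% are significantly lower. At k = 1.5 about 42% are higher. With mean thickness removed, both directions return to about 2.5%. In the last row the higher-order difference changes sign when mean thickness is not removed.

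**Simulation 2.** 60 versus 240 children, G = 0.40, W = 0.10. At k = 1.3, z rises by 0.16 in every network and 19% of pairs are falsely higher. At k = 0.8, z falls by 0.10 in every network. Removing mean thickness returns both to nominal.

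**What the adjustment can do to a real effect (set-up of simulation 2).**
- Sensory regions load more strongly on the common factor (1.4 versus 1), with the factor's own variance equal in both groups. The sensory difference is +0.21 unadjusted and 0.00 adjusted: a real difference confined to sensory networks disappears.
- The sensory network variance rises from 0.1 to 0.3. The difference is +0.12 unadjusted and +0.20 adjusted: its size changes although no artefact is present.

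**The case against.** The strongest reply is that the hypothesis has two halves of opposite sign, and a uniform shift contradicts one of them. That stands. A reader might infer that the network-specific hypothesis cannot be told apart from a global difference at all; the documents do not support this. Both sets of networks are outcomes, so a rise everywhere would be visible in the planned results. Even with unequal global loadings (1.3 sensory, 0.7 higher-order), the higher-order networks still rose, by 0.11, at a ratio of 1.3. What remains is that either half reported alone is open to this explanation, and that a true half can be hidden or reversed.

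Secondly, nothing in the SAP shows that overall thickness varies more in the deficit group. A reader might infer an upward bias; the ratio could as well be below 1. Ratios of 1.2 and 1.3 already mean 44% and 69% more global variance (1.2² = 1.44, 1.3² = 1.69). This stands, and it is why both directions are shown.

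Thirdly, covariance without global adjustment is a legitimate quantity, and adjustment gives a different one. Under one set of assumptions, within-network r fell from 0.50 to about 0.14 once mean thickness was removed. This also stands, and it rules out replacing the planned correlations.

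Finally, the word introducing the adjustment list leaves it open. That permits a global term but does not commit the plan to one.

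**Conclusion.** The point holds in limited form. The covariance comparison contains no term for overall thickness and no between-network contrast, while the hypothesis is about specific networks. A group difference in global spread alone moves every network the same way, so each half of the prediction, read alone, is confounded. The joint pattern is not confounded in this way.

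For a ratio of 1.3 the shift is about 0.09 to 0.16 in Fisher z across the assumptions tried; for 0.8 it is about −0.08 to −0.10. These figures rest on a one-factor global model, assumed variance shares and assumed group sizes. They ignore the SAP's restriction of the z-test to significant connections. The actual bias may be nil, and its direction is unknown, until the group SDs of mean thickness are reported.

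This is a worthwhile addition to the plan. It does not show that the planned correlations are invalid.

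**What to change.** In the section on constructing the networks, keep the planned correlations and add, before analysis:

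1. A second run that also partials out each child's mean cortical thickness. For subcortical volumes, use an analogous whole-brain or intracranial size term.
2. Both versions side by side, with the SD of mean thickness in each group.
3. A sensory-versus-higher-order contrast of the group differences in Fisher z. Pairs share children and regions, so obtain its interval by resampling children within groups. The contrast is not fully immune if global loadings differ: at a ratio of 1.3, networks with G = 0.40 and G = 0.20 shift by 0.152 and 0.093, leaving 0.152 − 0.093 = 0.059. It should therefore be read with item 1.
4. A sentence stating that a difference is called network-specific only with reference to these results.

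Do not admit networks to the 12-year step only if the difference keeps its direction and size after adjustment. The two versions are on different scales, and adjustment can remove a real sensory-only difference.

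While editing, state whether scanner site is adjusted for here, since it is another possible source of variation in overall thickness.

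The cost is one derived thickness variable, a size term for the volumes, one repeat run and one contrast. The adjusted correlations will be smaller and must be described as relative to the child's own mean.
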